### Conventional Intervention

We stipulate a protocol that considers motor physiotherapy conducted for 10 min, which will be performed at the bedside with mobilization exercises to activate the upper and lower limbs, orthostatic training, static and dynamic balance, and walking through the corridor.

### Virtual Intervention

During the protocol, the participants will perform tasks in a non-immersive VR environment for 10 min. Thus, we will use the MoveHero game (for details and publication, see Martins et al., 2019) that provides mobilization exercises to activate the upper and lower limbs, orthostatic training, and static and dynamic balance. The software that will be used was developed by the Research Group and Technological Applications in Rehabilitation group from the School of Arts, Sciences, and Humanities of the University of São Paulo and can be accessed at www.movehero.com.br/en.

#### MoveHero

MoveHero, as presented by Martins et al. (2019), is a game that displays falling spheres in four imaginary columns on the computer screen, with a musical rhythm selected by the researcher. This is also considered a coincident timing task; the action is to react (using the upper limbs) and not let the balls pass the fixed targets. The spheres should only be intercepted when they reach the targets allocated in parallel (at two height levels), two on the left (left position targets A and B) and two on the right of the participant (right position targets C and D), as shown in Figure 1. The virtual contact is performed by the avatar of the individual, i.e., a representation of the individual appears on the computer screen. The individuals move their arms and trunk (only if they can move the trunk) in front of the webcam to coincide with the moment the ball touches the target. The individual is positioned at a distance of ~1.5 m from the computer monitor and waits for the balls (which fall randomly on each target) to drop. The avatar's hand should reach the target sphere along with the arrival of the ball, and the game offers feedback on correctness and error by means of changing the spheres' color (green for correct and a red line for error).

**Figure 1 F1:**
[figure not shown]
Representative design of the MoveHero software performed during treatment intervention, with representation of hits (bottom left figure) with sphere turning into blue with stars, and misses (bottom right figure) with a red X.

Thus, the participants will play the MoveHero game in a bedside standing or seated position (depending on the patient's capacity), where they have to move their arms and body/trunk to catch the falling spheres. After this motor intervention, the participants will also receive respiratory physiotherapy for 10 min, during which they will perform exercises of respiratory reeducation.

### Procedure

Immediately before the beginning of each therapy (virtual intervention or conventional intervention), two assessment scales will be made (BORG Scale, Visual Analog Scale) and four physiological assessments [HRV, Spo_2_, RR, and HR]. Group A will start the first day of the protocol with virtual intervention (in the morning) and then in the second period (in the afternoon) will perform the conventional intervention, and Group B will perform the reverse protocol, in a crossover format. It will be applied for up to 8 consecutive days. On the last day, assessment scales will be repeated in a separate room, as well as the physiological assessments. After 7 days and 1 month of hospital discharge, all assessment scales will be undertaken at patients' homes, and the virtual intervention will be applied again (Figure 2).

**Figure 2 F2:**
[figure not shown]
Study design.

### Primary Outcome

We will observe changes in the ANSs after intervention with VR and conventional therapy in inpatients with COVID-19, during hospitalization and after 7 and 30 days of follow-up after hospital discharge.

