Key inclusion and exclusion criteria	Inclusion criteria: Agreement to participate in the research from themselves by signing consent form, a clinical and posterior blood analysis of COVID 19 infection, adults with age ranging from x to xx years. Exclusion criteria: Do not understand the tasks; the understanding of the task will be evaluated through five attempts at each task in virtual reality; do not want to use virtual reality task; was not in a physical condition to practice a functional task; use of an intravenous device that makes it impossible to move the arms; cardiac arrhythmias and atrioventricular block; congenital anomalies, such as congenital heart defects, pulmonary malformations; and patients who use drugs that interfere with ANS, such as antiarrhythmic agents
Study type Interventional allocation	Randomized
Masking	Randomization and data analyst
Assignment	Crossover
Primary purpose	Treatment
Date of first enrolment	June 2020
Target sample size	50
Recruitment status	Recruiting
Primary outcome(s)	Functional capacity improvement
Key secondary outcome(s)	HRV improvement

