### Recruitment

Fifty participants will be recruited through the Hospital of the Federal University of São Paulo (Hospital São Paulo) located in São Paulo State, Brazil. Those interested in participation will undergo a detailed screening using the eligibility criteria for enrolment in the study. The sample size was calculated using a statistical software (G^*^Power 3.1.5) on the main outcome measure (i.e., the motor score). This calculation was based on data from five patients (pilot study). The power was 0.80; the α was 0.05, and the effect size was 0.65 (Cohen *d*). The sample estimation indicated that 40 participants would be necessary (i.e., 20 per group), and with an adjustment to allow for a withdrawal rate (20%), we will recruit 50 participants.

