### Secondary Outcome

We will analyze changes in mood, satisfaction, and enjoyment regarding the interventions, RPE, and functionality in both interventions.

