### Statistical Analysis

Statistical analysis will be performed using IBM-SPSS (version 26.0, IBM Corp., Armonk, NY, USA). As dependent variables, all HRV indices will be considered, as well as test scores of Barthel Index, TUG, MRC, BRUMS, ES, VASS, Borg Scale, Sao_2_, RR, and HR. If the data meet the assumptions of normality, multiple analysis of variance will be used to compare the study groups (virtual group and conventional group) and intragroup comparison (virtual and conventional groups, when comparing the same subject), with least significant difference *post-hoc* test. If the data do not meet the assumptions of normality, the differences between the groups will be analyzed using the Kruskal–Wallis test. Dunn *post-hoc* tests will be performed on each pair of groups, with Dunn–Bonferroni post-test on each pair of groups. The same tests will be applied for *p* < 0.05, which will be considered significant.

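### The article gives contradictory primary outcomes (functional capacity in Table 2, autonomic change in the Methods), and neither is reduced to one variable, contrast and time

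*Protocol article*

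**What the plan says.** All of this is in the protocol article.

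- **Table 2** gives the primary outcome as "Functional capacity improvement" and the key secondary outcome as "HRV improvement". It also gives first enrolment as June 2020 and the status as recruiting.
- **Primary Outcome**: "We will observe changes in the ANSs after intervention with VR and conventional therapy in inpatients with COVID-19", observed "during hospitalization and after 7 and 30 days of follow-up after hospital discharge". The Heart Rate Variability section states that HRV is the means of analysing the autonomic nervous system (ANS).
- **Secondary Outcome** covers mood, satisfaction and enjoyment, followed by "RPE, and functionality in both interventions".
- **Recruitment** bases the sample size "on the main outcome measure (i.e., the motor score", with power 0.80, alpha 0.05 and d = 0.65. The motor score is not defined as an instrument. The Motor Function section assigns three tests to functional capacity: Barthel Index, TUG and MRC.
- **Statistical Analysis**: "As dependent variables, all HRV indices will be considered", together with ten other measures. If the data are normal, the section plans a multiple analysis of variance "with least significant difference" as the post-hoc test. If they are not, it plans Kruskal-Wallis with Dunn and Dunn-Bonferroni comparisons over pairs of groups. The threshold is p < 0.05 throughout.

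**The concern.** A primary outcome fixes in advance which result decides the trial. Here two parts of the same current document assign that role to different domains, each making the other's primary a secondary. Neither statement is marked as superseded, and patients were already being enrolled.

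The second difficulty lies within each domain. Functional capacity is three tests. The ANS outcome names no index and no contrast, and it spans three periods. With every HRV index tested at 0.05 and none ranked first, a favourable index could be put forward as the primary finding. A reader of the results could not tell whether it had been chosen beforehand.

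**Working it through.** **1. The plan's own figure.** The withdrawal step reproduces: 40 / (1 - 0.20) = 50. The 40 does not identify the intended variable or contrast. At d = 0.65, power 0.80 and two-sided alpha 0.05, a two-group t test needs 39 per group (78 in total) and a paired test needs 21 patients. Neither gives 40. That mismatch is a separate matter and nothing below depends on it.

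**2. The statements side by side.**

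| Place | Functional domain | ANS / HRV |
|---|---|---|
| Table 2 | primary | key secondary |
| Primary and Secondary Outcome sections | secondary | primary |
| Recruitment (sample size) | possibly, as a motor score | no |
| Statistical Analysis | Barthel, TUG and MRC listed, unranked | all indices listed, unranked |

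The first two rows cannot both hold. The third fits Table 2 only if the motor score is one of the functional tests, or some combination of them, and the article does not say so.

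**3. Chance of a false positive among HRV indices.** The article mentions time-domain, frequency-domain and non-linear HRV analysis but gives no number of indices. I assume k = 5 to 15, one contrast at one time, each tested two-sided at 0.05, with no true effect.

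- Independent tests: 1 - 0.95^k. For k = 5, 1 - 0.774 = 0.226; for k = 10, 1 - 0.599 = 0.401; for k = 15, 1 - 0.463 = 0.537.
- Correlated tests: simulation of equally correlated normal statistics (200,000 draws), counting draws in which any |Z| exceeds 1.96.

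| k | independent | correlation 0.5 | correlation 0.8 |
|---|---|---|---|
| 5 | 23% | 18% | 13% |
| 10 | 40% | 29% | 17% |
| 15 | 54% | 36% | 20% |

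**4. Role of the post-hoc test.** Two interventions form one pair. With one pair there is nothing to adjust, so least significant difference and Bonferroni coincide. The choice matters only over three or more levels. Table 1 marks HRV at four times (t1, t8, t9, t10), which gives 4 × 3 / 2 = 6 pairs per index. Six independent tests would give 1 - 0.95^6 = 26%; pairs sharing time points are not independent, so this is only indicative.

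**5. Which measurements can carry the contrast.** Both groups are planned to receive both interventions on each treatment day, in opposite order. A value at the end of the stay, or at 7 or 30 days, therefore follows both. Comparing Groups A and B at those times compares sequences, and no within-patient difference between interventions can be formed. Only a measure taken around each session can do that.

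Table 1 schedules Barthel, TUG and MRC at the start, the end of the stay and follow-up, not around sessions. For HRV the article is inconsistent:

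- Heart Rate Variability section: before, during and after the intervention.
- Procedure: immediately before each therapy.
- Assessment Protocol: in the initial assessment, but absent from the list taken before and after each intervention.
- Table 1: t1, t8, t9 and t10 only.

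**The case against.** The strongest defence is that an article condenses a fuller plan, and that the HRV index and a multiplicity rule are often left to an SAP. That is fair as far as naming the index goes. It does not explain two opposed primaries in one text, and an SAP cannot show which published statement governs. The unranked list at p < 0.05 is also something the article itself fixes.

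A second defence is that multiple analysis of variance may mean MANOVA, which gives one joint test over the indices. On that reading a joint test exists, but the article does not make the later tests conditional on it.

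Five stronger readings are tempting and are not supported:

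- *Three different primaries.* Because functional capacity sits under the Motor Function heading, the motor score may be in the same domain as Table 2's primary. Two domains certainly conflict; the third label is undefined.
- *The Methods primary is all HRV indices.* The Primary Outcome section does not say so. The phrase comes from the list of dependent variables, and the link to the primary runs through the HRV section.
- *Unadjusted LSD is the main fault.* Step 4 shows that it is not, for the treatment comparison.
- *A false-positive chance of 79%.* That is 1 - 0.95^30, from ten assumed indices at three times, all independent. Neither the ten nor the independence is given, and the two follow-up visits supply no within-patient treatment contrast.
- *The sample size supports no outcome.* If the motor score is a functional test, it addresses Table 2's primary, and 40 patients give 98% power on a paired reading at d = 0.65. What can be said is that it was not calculated for the ANS outcome or for a defined instrument.

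**Conclusion.** The contradiction is certain, concerns what the trial will conclude, and must be resolved in this document. Table 2 and the Primary and Secondary Outcome sections exchange the two domains, the sample size rests on an undefined label that is not the ANS outcome, and neither domain is narrowed to a single variable.

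The size of the error-rate problem is conditional. Over the assumed 5 to 15 indices, for one contrast at one time, it runs from 13% (5 indices, correlation 0.8) to 54% (15 indices, independent), against a nominal 5%. HRV indices are likely to be correlated, so the independent column is best read as the upper end. The inflation comes mainly from the number of unranked indices. A reader might infer that outcomes were in fact selected after data were seen. The article does not show that; it shows only that its wording would allow it.

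**What to change.** The sponsor should name one primary variable, one contrast (VR versus conventional) and one time, and use them identically in Table 2, Recruitment, Primary Outcome and Secondary Outcome. Which domain becomes primary is the sponsor's choice.

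- The contrast should use a measure taken around each session. If an HRV index is chosen, Table 1 and the Heart Rate Variability, Assessment Protocol and Procedure sections must be reconciled on when HRV is recorded. If a functional test is chosen, its present schedule does not supply the within-patient contrast, and the plan must say how one is obtained.
- Test that primary alone at 0.05. Label the other HRV indices and scales either secondary, with a stated multiplicity adjustment, or exploratory.
- Restate the sample-size basis for the chosen primary. The d = 0.65 belongs to the motor score and does not carry over to HRV without justification.
- Disclose which statement was changed, and that enrolment began in June 2020.

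The cost is protocol wording, the registry entry where it carries the changed wording, a restated sample-size basis, and secondary claims that are slightly harder to make. If the chosen variable is not already recorded around each session, the assessment schedule changes as well.

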### Secondary Outcome

We will analyze changes in mood, satisfaction, and enjoyment regarding the interventions, RPE, and functionality in both interventions.

### Statistical Analysis

Statistical analysis will be performed using IBM-SPSS (version 26.0, IBM Corp., Armonk, NY, USA). As dependent variables, all HRV indices will be considered, as well as test scores of Barthel Index, TUG, MRC, BRUMS, ES, VASS, Borg Scale, Sao_2_, RR, and HR. If the data meet the assumptions of normality, multiple analysis of variance will be used to compare the study groups (virtual group and conventional group) and intragroup comparison (virtual and conventional groups, when comparing the same subject), with least significant difference *post-hoc* test. If the data do not meet the assumptions of normality, the differences between the groups will be analyzed using the Kruskal–Wallis test. Dunn *post-hoc* tests will be performed on each pair of groups, with Dunn–Bonferroni post-test on each pair of groups. The same tests will be applied for *p* < 0.05, which will be considered significant.

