According to Bond et al. (2019), the requirement of physical exercise inherent to a video game's activities (exergames) is shown to have a promising impact in improving patient self-efficacy for exercise training using digital hardware (e.g., the Nintendo Wii® or the Xbox Kinect®), once interactive VR promotes increased heart rate (HR), rating of perceived exertion (RPE), and physical activity (Bond et al., 2019; García-Bravo et al., 2019). Therefore, patients using exergames rather than conventional exercise routines (e.g., walking, running, or cycling) have been reported to exercise for longer periods, meeting moderate to vigorous physical activity levels, with the perception of “work” being lower or less intense, and more enjoyable, contributing to healthier lifestyle initiatives (Glen et al., 2017; Gomez et al., 2018; Polechoński et al., 2019).

Considering the above deliberations, we have organized a randomized controlled crossover protocol to investigate rehabilitation of patients hospitalized with COVID-19. The aim of this protocol is to find out whether the motor performance, functionality, engagement, motivation, and physiological parameters are different during conventional or virtual intervention. We are interested in comparing conventional cardiovascular and musculoskeletal physical therapy interventions with typical movements and mobilization in different postures such as sitting and standing, using VR software that provides a game in which the participants continually move upper limbs and trunk to finish a motor task proposed by the application. Participants will therefore alternate their rehabilitation intervention (conventional or virtual) during their hospitalization period. Furthermore, we will be using a satisfaction scale to verify the level of engagement in the therapy during the rehabilitation program.

We hypothesize that all participants will show improvement in motor performance, functionality, and physiological parameters independent of the intervention (conventional or virtual environment); however, the use of a virtual task will provide more engagement and motivation. If our hypothesis is proven, it might be the beginning of a technological innovation in cardiorespiratory rehabilitation in hospitals.

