##### Brunel Mood Scale

This scale was developed to allow a quick measurement of the mood of adults and adolescents. BRUMS contains 24 simple mood indicators, such as feelings of anger, disposition, nervousness, and dissatisfaction that are noticeable by the individual being assessed. The evaluated responds to the scale according to how they feel about such sensations. The score is 5 points (0 = nothing to 4 = extreme). The question format is “How do you feel now,” although other forms: “How have you felt this past week, including today” or “How do you normally feel” can be used. BRUMS takes about 1 to 2 min to complete. The 24 indicators of the scale comprise six subscales: anger, confusion, depression, fatigue, tension, and vigor (Rohlfs et al., 2008; Sties et al., 2014).

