##### Heart Rate Variability

We will use HRV to analyze ANSs before, during, and after the intervention for recovery assessment. The analysis will follow the guidelines of the (Heart rate variability: standards of measurement, physiological interpretation and clinical use. Task force of the European Society of Cardiology and the North American Society of pacing and electrophysiology, 1996). The strap (for data collection) will be positioned on the participant's chest, and the Polar V800 (Polar Electro, Finland) HR receiver will be positioned next to it. HRV will be recorded after the initial assessments at rest for 20 min. For analysis of HRV data at rest, 1,000 consecutive resting rate intervals will be used (da Silva et al., 2018; Moraes et al., 2019). Heart rate will be recorded beat by beat throughout the protocol by the Polar V800 HR receiver, and resting rate intervals recorded by the monitor will be transferred to the Polar ProTrainer program, which allows HRV visualization and cardiac period extraction in the “txt.” file format.

Moderate digital filtering will be performed in the program itself. HRV analysis will be performed using linear (time and frequency domain) that will be analyzed using Kubios HRV® software (Kubios HRV v.1.1 for Windows, Biomedical Signal Analysis Group, Department of Applied Physics, University of Kuopio, Finland) and non-linear methods (Vanderlei et al., 2009).

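### All outcomes are listed together as dependent variables of a multiple analysis of variance, and on neither reading of that phrase is one test tied to the primary autonomic question

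*Protocol article*

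**What the plan says.** The Statistical Analysis section gives one list of dependent variables: "As dependent variables, all HRV indices will be considered, as well as test scores of Barthel Index, TUG, MRC, BRUMS, ES, VASS, Borg Scale", followed by oxygen saturation, respiratory rate and heart rate. For normal data, "If the data meet the assumptions of normality, multiple analysis of variance will be used to compare the study groups", together with an "intragroup comparison (virtual and conventional groups, when comparing the same subject), with least significant difference" follow-up. For non-normal data it uses Kruskal–Wallis and Dunn tests. The threshold is 0.05 throughout.

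The Primary Outcome section covers one domain: "We will observe changes in the ANSs after intervention with VR and conventional therapy in inpatients with COVID-19". Mood, satisfaction, enjoyment, perceived exertion and functionality are secondary. Table 2, however, gives the primary outcome as "Functional capacity improvement" with HRV as key secondary, and the Recruitment section sizes the trial on a motor score.

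The Introduction expects motor, functional and physiological gains under either intervention; "however, the use of a virtual task will provide more engagement and motivation".

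The Heart Rate Variability section plans time-domain, frequency-domain and non-linear indices ("HRV analysis will be performed using linear (time and frequency domain" and so on). It gives no count and singles out no index.

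**The concern.** A MANOVA over this list tests whether the whole vector of outcome means is equal under the two interventions. The primary question is narrower: does autonomic function differ? If the investigators are right that engagement differs and physiology does not, the omnibus null is false while the HRV null is true. A significant result would then say nothing about HRV. In the other direction, a real effect on one HRV index is spread over many unaffected variables and may be missed.

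If separate ANOVAs are meant, the omnibus problem disappears. What remains is ten or more tests at 0.05, followed by unadjusted least-significant-difference comparisons, with none marked as the test of the primary outcome.

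**Working it through.** **Inputs from the protocol.** Effect size d = 0.65, power 0.80, alpha 0.05, 40 evaluable patients (20 per group) and 50 recruited (Recruitment). The inflation reproduces: 40/(1 − 0.20) = 50. The 0.65 belongs to the motor score and is borrowed here for HRV only as a scale. The 40 does not follow from a plain two-sided t-test at d = 0.65 (78 in total for two groups, 21 for pairs). That is a separate matter.

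**Number of variables, p.** Ten scores are named besides HRV. The Brunel Mood Scale section says: "The 24 indicators of the scale comprise six subscales: anger, confusion, depression, fatigue, tension, and vigor". Counting these six separately gives 10 − 1 + 6 = 15 before any HRV index. The HRV count is not given, so I take p = 15 to 30.

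**Single-variable test.** Noncentral t, two-sided: 98% power with 40 pairs, 52% with 20 per group.

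**MANOVA with one HRV index shifted.** Hotelling's T², power from the noncentral F:
- within patient: df (p, n − p), noncentrality n·D²;
- between groups: df (p, 2n − p − 1), noncentrality (n/2)·D²;
- D² = 0.65² × [1 + (p − 2)ρ] / {(1 − ρ)[1 + (p − 1)ρ]}, where ρ is an assumed common correlation.

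Example, p = 20, ρ = 0.3, 40 pairs: D² = 0.4225 × 6.4/(0.7 × 6.7) = 0.577; noncentrality 40 × 0.577 = 23.1; critical F(20, 20) = 2.12; power 52%.

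| p | 40 pairs, ρ = 0 | ρ = 0.3 | ρ = 0.5 | ρ = 0.7 | 20 per group, ρ = 0.3 |
|---|---|---|---|---|---|
| 15 | 51% | 67% | 85% | 98% | 17% |
| 20 | 38% | 52% | 71% | 93% | 13% |
| 25 | 27% | 38% | 53% | 81% | 11% |
| 30 | 18% | 25% | 35% | 58% | 8% |

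**Several HRV indices shifted.** With 40 pairs, five indices each shifted by 0.65 and ρ = 0.3 throughout, power is 100%, 99.8% and 98% for p = 15, 20 and 25. With correlation 0.6 among those five it is 92%, 82% and 66%. Between groups of 20, with six indices shifted and p = 16, it is 69% at ρ = 0 and 98% at ρ = 0.7, above the single-variable 52%.

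**HRV unaffected, two engagement scores shifted by 0.65.** With 40 pairs and ρ = 0.3, the MANOVA rejects in 95%, 86%, 71% and 49% of trials for p = 15, 20, 25 and 30.

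**Separate ANOVAs.** If the tests were independent, the chance of at least one false positive is 1 − 0.95^10 = 0.40 for 10 tests and 1 − 0.95^16 = 0.56 for 16.

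**Can the joint vector be formed?**
- Barthel, TUG, MRC and BRUMS are taken at the start (enrolment or day 1), on day 8 and at follow-up (Table 1). By the end of the stay every patient has had both therapies (Overview of the Study Design), so these scores have no separate VR and conventional values.
- ES and VASS are completed at the end of each day, after both sessions (Assessment Protocol). The Enjoyment Scale and Procedure sections give other timings.
- Borg, saturation, respiratory rate and heart rate are taken before and after each session.
- HRV is recorded around each therapy according to Heart Rate Variability and Procedure. Table 1 marks it only on day 1, day 8 and at the two follow-ups. Both therapies are given on day 1, so a paired HRV comparison is possible there on either account.

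One complete vector per intervention therefore does not exist for about half of the named scores.

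**The case against.** The strongest reply is that a single MANOVA was never meant. The section does not say multivariate. The branch for non-normal data (Kruskal–Wallis) is univariate, and so is the least-significant-difference follow-up. The impossibility of forming the joint vector points the same way. This stands as a real ambiguity. It does not rescue the plan, because separate ANOVAs still leave no test assigned to the primary question.

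A reader might infer that the trial would falsely claim an HRV effect in up to 95% of cases. The document does not support that. Those are correct rejections of a false omnibus null. They mislead only if reported as an HRV result, and no rule says the omnibus p-value decides the primary outcome or gates the rest.

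A reader might also infer that most of the power for HRV is lost. That is not general. It holds between groups with one affected index and low correlation. Within patients the loss runs from nearly none to severe, depending on the correlation and on how many indices move.

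Nor can one say that the test misses the effect the trial was planned on, since 0.65 was set for the motor score. Finally, the paired figures presuppose a vector that cannot be built for many scores. They show what a MANOVA would do if it could be run.

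**Conclusion.** The concern holds in this form: the section pools all outcomes under a procedure with two possible meanings, and neither fixes one test of the primary question. Read as a MANOVA, it tests a different hypothesis from the stated one, can reject for the reason the investigators themselves predict, and can cost much of the power for a single HRV index. The number of HRV indices, the correlations and the use of d = 0.65 for HRV are assumptions. The mismatch of hypotheses depends on none of them. The conflict over which outcome is primary (Primary Outcome, Table 2, Recruitment) must be reconciled, but whichever is chosen, a pooled test would not isolate it.

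**What to change.** In Statistical Analysis:
1. Replace the pooled multivariate test with a separate univariate analysis of each outcome, using every patient who has that outcome.
2. Name one HRV index and one time point, and judge the autonomic question only by its within-patient comparison of VR and conventional sessions. Bring Table 1, Heart Rate Variability and Procedure into agreement on when HRV is recorded.
3. Reconcile the primary outcome across Primary Outcome, Table 2 and Recruitment, and treat all other outcomes as secondary.
4. Use the within-patient contrast only for measures taken per session. Report scores taken at the start and end of the stay as change over the stay, not as a comparison of interventions.
5. For engagement, either record ES and VASS after each session or make no intervention claim from end-of-day scores.

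Items 1 to 4 change wording only, with the same data and software. The first option in item 5 adds one more completion of two short scales per day and helps only patients not yet treated; the second costs nothing to collect but gives up the test of the engagement hypothesis. The one statistical loss is a global test across outcomes, which no stated objective uses.

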##### Respiratory Rate and Heart Rate

Respiratory rate (RR) and HR will be measured before starting and at the end of both VR and conventional interventions.

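### The stated analysis makes no use of the pre-treatment values the trial collects, which costs precision and leaves chance baseline imbalance in the estimates

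*Protocol article*

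**What the plan says.** The Statistical Analysis section fixes the dependent variables: "As dependent variables, all HRV indices will be considered, as well as test scores of Barthel Index, TUG, MRC", followed by the mood, enjoyment, satisfaction, exertion and vital-sign measures. It then fixes the model: "multiple analysis of variance will be used to compare the study groups (virtual group and conventional group"), together with a comparison within the same subject. Kruskal–Wallis with Dunn tests is the fallback for non-normal data. The section mentions no baseline covariate, change score or pre/post factor.

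Pre-treatment values are planned elsewhere in the article:

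- Table 1 and the Assessment Protocol place Barthel at enrolment, and TUG, MRC, BRUMS and HRV at the start of the protocol.
- The Assessment Protocol has Borg, SpO2, respiratory rate and heart rate taken on both sides of every session. For the last two, the Respiratory Rate and Heart Rate section confirms that they "will be measured before starting and at the end of both VR and conventional interventions".
- The Procedure section says "Immediately before the beginning of each therapy (virtual intervention or conventional intervention), two assessment scales will be made", and adds HRV, SpO2, respiratory rate and heart rate at the same moment.

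The Primary Outcome section is worded as change: "We will observe changes in the ANSs after intervention with VR and conventional therapy".

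**The concern.** Patients admitted with COVID-19 are likely to differ widely in HRV, TUG, MRC and Barthel before any session. A model without the starting value leaves that spread in the error term. With 20 to 25 patients per group, a chance difference at baseline also carries into the estimated group difference. The Randomization section screens balance on age and Barthel only, so HRV, TUG and MRC are unprotected. Age and Barthel are forced to balance and then left out of the model, which makes the standard error larger than it need be if they predict outcome.

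The rank fallback makes matters worse. Kruskal–Wallis treats the observations as independent and cannot take a covariate. If normality fails, the session measures lose both the benefit of pairing and any chance of adjustment.

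**Working it through.** **Inputs.** From Recruitment: d = 0.65, alpha 0.05, power 0.80, 20 per group, 50 recruited. The calculation was made "on the main outcome measure (i.e., the motor score"), so its use for HRV is illustrative only. Sidedness is not stated; two-sided is assumed. Rho, the baseline-to-outcome correlation, is not given; 0.3 to 0.7 is assumed.

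**The plan's own figure.** The dropout step reproduces: 40 / 0.8 = 50. The 40 does not reproduce as a two-group size. A two-sided two-sample t-test at d = 0.65 and 80% power needs 39 per group. At 20 per group the noncentrality is 0.65 × √(20/2) = 2.06 and power is 51.7%. That figure is the unadjusted reference below.

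**Group A versus Group B, with and without baseline.** A baseline covariate multiplies the residual SD by √(1 − rho²), so the effective d is 0.65/√(1 − rho²), with one degree of freedom lost. For an unadjusted change score the effective d is 0.65/√(2(1 − rho)).

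| rho (assumed) | Residual SD multiplier | Effective d, covariate | Power, 20 per group | Power, 25 per group | Power, change score, 20 per group |
|---|---|---|---|---|---|
| no adjustment | 1 | 0.65 | 51.7% | 61.5% | – |
| 0.3 | 0.954 | 0.681 | 55.5% | 65.5% | 39.5% |
| 0.5 | 0.866 | 0.751 | 63.7% | 73.9% | 51.7% |
| 0.7 | 0.714 | 0.910 | 80.0% | 88.3% | 73.4% |

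At 20 per group the covariate adds 3.8, 12.0 or 28.3 points. The residual SD multiplier does not depend on d: residual SD falls by about 5%, 13% or 29%, and that part applies to HRV as much as to the motor score. The unadjusted change score is not a safe substitute. It gains nothing at rho 0.5 and loses about 12 points at rho 0.3 (51.7 − 39.5 = 12.2).

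**Same-subject comparison.** Every patient receives both therapies. With 40 patients, d = 0.65 on the between-patient SD and within-patient correlation r, the paired effect is 0.65/√(2(1 − r)). Power is 80.9% at r = 0, 92.3% at r = 0.3 and 98.0% at r = 0.5. The room left for any gain in power is therefore 19.1, 7.7 or 2.0 points. A baseline measured once per patient has the same value under both therapies and cancels from the difference. Only a baseline specific to each session can add precision.

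**Which contrast each outcome supports.** Table 1 schedules Barthel, TUG, MRC and BRUMS at the start, at t8 and at follow-up. By then each patient has had both therapies. These outcomes have no separate virtual and conventional value, and their only randomised contrast is Group A against Group B, which is a contrast of order.

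**Availability of the HRV baseline.** The sections disagree. Table 1 has HRV at t1, t8 and follow-up only. The Heart Rate Variability section has it before, during and after the intervention. The Assessment Protocol lists it once at the start and leaves it out of the per-session list. The Procedure section puts it immediately before each therapy.

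**The case against.** The strongest reply is that choice of covariate is commonly left to a statistical analysis plan, which is not shown. The section never says that the variables are analysed raw, and its same-subject clause is loose enough to allow a pre/post factor. That lowers the weight of the point but does not remove it. The section is not silent: it commits to dependent variables, a model, post-hoc tests and a rank fallback, and the fallback cannot use a baseline at all.

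A reader might infer a fixed loss of about 12 points of power. The document does not support that. The figure needs an assumed rho of 0.5 and a 20-versus-20 parallel comparison, whereas all patients receive both therapies and a same-subject comparison is also planned.

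A reader might also infer that the analysis fails to estimate the change promised in the Primary Outcome section. That does not follow for the treatment contrast. Under randomisation, a difference in post-treatment values has the same expectation as a difference in change, so the loss is one of precision and protection from chance imbalance.

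It is also fair to say that imbalance is limited for Barthel, which the Randomization section forces to balance, and that stable patient differences cancel in a same-subject comparison.

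**Conclusion.** The point holds as one of efficiency. The stated analysis leaves out pre-treatment values that the trial collects, and its rank fallback discards pairing as well. The size of the loss cannot be fixed from the document. For Group A versus Group B at 20 per group, d = 0.65 and two-sided 0.05, the covariate would add about 4 to 28 points of power for assumed rho of 0.3 to 0.7. In the same-subject comparison there is less to gain, and only session-specific baselines can supply it. The calculation is illustrative for HRV. Adjusting Barthel, TUG, MRC or BRUMS sharpens a comparison of treatment order and does not turn it into a comparison of virtual with conventional therapy. That the planned 40 does not reproduce as a two-group size is a separate matter.

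**What to change.** In the Statistical Analysis section, state how pre-treatment values enter each model.

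- **Measures taken around each session** (Borg, SpO2, respiratory rate, heart rate, and HRV once its timing is reconciled across Table 1, Heart Rate Variability, Assessment Protocol and Procedure): fit a linear mixed model of the after-session value. Fixed effects are treatment, period (morning or afternoon), sequence and the before-session value; patient is a random effect. Log-transform skewed HRV indices instead of switching to Kruskal–Wallis.
- **Sensitivity analysis:** the afternoon before-session value may carry the effect of the morning session, so refit without the before-session covariate. Using the morning reading as covariate for both sessions would not serve, because it cancels from the within-day contrast.
- **Barthel, TUG, MRC and BRUMS:** adjust any Group A versus Group B comparison for the enrolment or t1 value, and state that it compares treatment order.

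The cost is wording, one covariate per model and one sensitivity run. Borg, SpO2, respiratory rate and heart rate are already planned on both sides of each session. For HRV, the cost depends on which recording schedule is actually in use.
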